## Abstract

**Background:**

Family group conferences (FGCs) in child welfare bring immediate and wider family members together to decide on the best way to meet a child’s needs. Unlike professionally led meetings, the aim is for decisions to be made by or with family members. Qualitative and mixed-method research with FGC participants tends to show positive experiences: most participants feel their voices are heard; FGCs facilitate family-driven solutions and closer relationships—within families and with social workers. Although there is existing literature on FGCs, there is a paucity of robust comparative UK evaluations, i.e., randomised controlled trials or quasi-experimental studies. Comparative studies internationally have focused on a narrow range of outcomes, not recognised the importance of context, and paid little attention to the quality of delivery. Some qualitative studies have considered process and context but there is scant measurement of these. The aims of this study are, firstly, to establish how FGCs improve outcomes for families and what factors vary their quality, and, secondly, to assess longer-term outcomes in terms of service use and associated costs.

**Methods:**

Given the importance of process and context, evaluation informed by realist and complex systems approaches is needed. This multi-method evaluation includes a survey of FGC services in all UK local authorities (n = 212) to map service provision; co-design of programme theory and evaluation measures with family members who have experienced an FGC (n = 16–24) and practitioners (n = 16–24) in two sites; a prospective single-arm study of FGC variability and outcomes after six months; and comparison of service use and costs in FGC participants (n≥300 families) and a control group (n≥1000) after two years using a quasi-experiment.

**Discussion:**

This is a pragmatic evaluation of an existing intervention, to identify what mechanisms and contexts influence effective process and longer-term outcomes. The study is registered with Research Registry (ref. 7432).

## Introduction

A family group conference (FGC) in child welfare brings immediate and wider family members, and others from their social network, together to decide on the best way to meet the needs of a child who requires support and/or protection. Unlike professionally led meetings, FGCs aim to shift decision-making to family members. They do so more fully than attempts to make traditional case conferences more strengths-based [1]. Staff who are termed ‘co-ordinators’ prepare potential attendees for the FGC meeting and usually facilitate the start of the meeting, but then professionals leave the room so that family network members only can have ‘private family time’ [2]. Children and young people sometimes attend themselves, but this depends on age and the family situation [3]. Sometimes children and young people are represented by advocates. FGCs originated in Aotearoa New Zealand, with a focus on Māori whanau (families) and in the context of concern about the over-representation of Māori tamariki (children) in state child welfare interventions [4].

There is also concern in many other countries about rising levels of state intervention, especially rising rates of children in out-of-home care [5]. There is concern about a professionally led child protection system which can be confrontational in style [6] and focused on forensic investigation at the expense of support for families [7]. In this context, FGCs are often seen as an important element of developing a child welfare system that is based on more positive relationships between the state and vulnerable families [8].

FGCs have the two primary aims of increasing family participation in important decisions about children and reducing more intrusive state intervention.

FGCs are widely used in the UK. There are likely to be similarities and differences in policy and provision between the four nations (England, Scotland, Wales, Northern Ireland), but there is no recent comparative study that maps these differences. The Family Rights Group, who promote and quality assure FGCs across the UK, estimated in 2019 that three-quarters of local authorities in England and Wales run or commission an FGC service or are planning to do so [9]. We roughly estimate, based on the referrals expected for the randomised controlled trial run in England by Coram (a children’s charity with an evaluation arm), that around 15,000 children in the UK or more may be involved in FGCs each year [10]. This is a rough estimate only, based on local authority projections of how many pre-proceedings cases they expected during the Coram trial.

Qualitative and mixed-method research with FGC participants suggests that most families who have had an FGC feel that they offer an increased opportunity for their voices to be heard; hence, they can be seen to facilitate family-driven solutions [6, 11]. FGCs have also been found to help foster closer relationships between family members and improve partnership working between social workers and families [12]. Fewer studies have focused on the experiences of children specifically, but these have also reported positive experiences, as well as some challenges [2, 13].

It is important, however, to compare families who have attended FGCs with similar families who have not, to see how outcomes and experience differ. Several randomised controlled trials and quasi-experimental studies have been conducted internationally, with 18 included in a recent systematic review [14] of all types of participative family meetings (FGCs and other models with different names). Only two of the FGC studies included in this review took place in the UK [15], and all the FGC studies had a high or moderate risk of bias. Most focused on reduction in out-of-home care, showing mixed evidence of effectiveness. A similar systematic review for the Campbell Collaboration [16] also found mixed evidence for this outcome. Other outcomes are important, given that FGCs are designed to increase family involvement as an important goal in its own right [17]. Few comparative studies of any type of participative family meeting have considered outcomes such as family satisfaction, family empowerment or engagement with support services [7, 8] but the evidence on effectiveness for these outcomes is also mixed and of low quality. These comparative studies tend to focus on outcomes to the exclusion of consideration of process and context.

The contrast in findings between different types of studies is interesting. It might be explained by selection effects, e.g., if family members with a more positive experience are more likely to volunteer for qualitative interviews that can be time-consuming, compared to questionnaire completion, for example. It is quite likely explained by most qualitative studies being conducted only with families who have had FGCs, and not with similar families who have experienced conventional services but no FGC. Asking the same questions of families with similar problems who have not taken part in an FGC but had more conventional professionally led meetings makes for a more valid comparison of people’s experience of FGCs. Also, a critical perspective is needed on concepts and measures used in studies–for example, some measures used for family empowerment may be capturing parental self-efficacy more than ownership of key decisions about children.

To some extent, it is unsurprising that the outcomes of a complex intervention will be mixed. However, Nurmatov *et al*. [14] conclude that one possible explanation for mixed effectiveness is variation in the quality of delivery. They note that ‘it is likely that there is considerable variation in how well shared decision-making meetings, and indeed treatment as usual services, are actually delivered’ and they go on to say that ‘it is very likely that the passion and skill with which services are provided has a substantial impact on the difference’ [13, p.41]. They found that few studies in their review reported on fidelity to the shared decision-making model and none reported on the quality of delivery of usual services. They recommended that future studies include evaluation of the actual service delivery in addition to outcomes.

Some studies suggest that families who have had FGCs do not differentiate the process itself and their engagement with it from the outcomes they experience [18]. Mitchell [19] found that family members’ personal experience of the FGC process impacts their perception of the relevance of support offered, their sense of empowerment and their perspectives on outcomes achieved. The aspect of FGCs often thought to be the most important process issue, namely families’ rights to participation being upheld [18] can also be conceived of as an outcome [20]. Considering this, it is important to work with families who have lived experience of FGCs, to establish what, for them, are the important outcomes of FGCs, before assessing how well these outcomes are met in practice.

Despite there being a sizeable literature on FGCs to date, there remain several key limitations and evidence gaps. There is a paucity of robust comparative evaluations in the UK context. Comparative studies internationally have focused on a fairly narrow range of outcomes with minimal recognition of the contextual contingency of effects and little attention to the quality of service delivery. Some qualitative studies have considered process, but these have not involved measurement of context and process variables. The research evidence on FGCs demonstrates some of the complexity of delivering the intervention. In light of this, a more nuanced, complex systems approach to evaluation is needed.

Our study involves co-design with service users; has a comparative element; and measures context and process as well as outcomes in the short, medium, and longer term. The study aims to establish how FGCs improve outcomes for families and what factors vary their quality. To do so, the study poses the following research questions (RQs). The respective work packages (WPs) are noted, with these described in detail in the following sections.

RQ1: What is the extent and nature of FGC provision for child welfare in the UK? (WP1)RQ2: How do families and practitioners see FGCs as impacting on families and what do they think might support or hinder their effectiveness? (WP1)RQ3: How does variation in the quality and implementation of FGCs impact on outcomes and acceptability? (WP2)RQ4: What are the longer-term outcomes of FGCs in terms of service use, e.g., child protection involvement and health care? How do these compare with similar families who have not taken part in FGCs and what are the economic consequences of FGCs? (WP3)

## Materials and methods

### Design and theoretical/conceptual framework

The study is informed by realist and complex systems thinking, integrating these into the well-established Medical Research Council approach for evaluating complex interventions, as demonstrated by Fletcher *et al*. [21]. Theorising intervention process and effects will move beyond the traditional, linear approach to modelling interventions and instead work with complex systems modelling, privileging context more clearly [22, 23]. In conceptualising context, we will draw on the framework of Pfadenhauer *et al*. [24].

It is a multi-method evaluation, including a survey to map service provision; qualitative co-design of programme theory and evaluation measures; a survey of family members at three time-points to assess process and self-reported outcomes; and a comparative study of longer-term service-use outcomes using linked routine administrative data. The study is registered with Research Registry (ref. 7432).

Project work packages:

WP1: Identification and modelling of FGCs in the UK; modelling programme theory and development of evaluation design (RQ1, RQ2)WP2: Prospective single-arm study of FGC variability and outcomes after six months (RQ3)WP3: Comparison of service use and associated costs in FGC participants and a comparison group after two years using a quasi-experiment (RQ4)

### Work Package 1 –Identification and description of FGCs in the UK; modelling programme theory; and development of evaluation design (RQ1 and 2)

WP1 will focus on understanding the local variations of FGCs within the UK context and on modelling the programme theory of the FGC as an intervention–i.e., determining its key mechanisms and outcomes, and the implementation contexts that have an impact on its effectiveness. This will support the identification of the most appropriate evaluation measures.

Three key activities will be undertaken as part of WP1: identification and description of FGC services (A); modelling of FGC programme theory (B); and co-design and piloting of evaluation tools (C).

#### A. Identification of FGC services in the UK

We will conduct a survey of local authorities and their equivalents across the UK to identify the current use of FGCs, and differences in practice and contextual factors between authorities. The aim of the survey is to describe the FGC landscape in the UK. It will not provide enough depth to inform the programme theory (B below), but the information gathered about FGC practice and contextual differences will be used in combination with the programme theory to inform the development of the evaluation measures (C below). Results from the survey will also inform local authority selection for WP3.

*Sampling*. The sample frame will comprise all local authorities in England, Scotland and Wales, and Health and Social Care Trusts in Northern Ireland (n = 212). Given that most authorities are likely to have implemented a related service at some point, all will be included in the sample frame. It will also be helpful to know about local authorities who have either never used FGCs and those who have disinvested in them.

*Setting/context*. Local authorities have statutory responsibility for child welfare in England, Wales, and Scotland. In Northern Ireland the equivalent bodies are Health and Social Care Trusts, but for brevity, we use the term ‘local authorities’ here in reference to all UK nations. They both provide their own services and commission services from the private and third sectors.

*Data collection*. An online survey will be developed in collaboration with the Family Rights Group and in consultation with experienced FGC practitioners. There are two routes to reaching FGC services. Firstly, we will send the online survey link to all heads of children’s services in the UK and ask them to cascade the survey to relevant staff, such as FGC service managers. Secondly, local independent FGC services will also be identified directly via a systematic web search (‘family group conference’ and each local authority name). Identified FGC services will also be emailed the survey link and asked to take part. Consent will be sought via a tick-box on the first page of the questionnaire. The anticipated respondents are FGC service managers but there will be no criteria imposed as to who can complete the questionnaire.

The online questionnaire will be fairly brief and focused, including questions about:

Whether or not FGCs are currently used in the local authorityWhether FGCs were offered in 2017–19 (the baseline period for WP3)The stage of child welfare concern when FGCs are offeredThe family circumstances for which FGCs are usedWhich kind of organisation delivers the FGCsWhether there is any theoretical model that informs the approach usedHow services have been functioning in light of Covid-19Number of conferences run each yearWhat data are currently recorded for evaluation purposes and how valuable this isStaff involved including contact details (for WP2)

There will be a mixture of fixed-response quantifiable questions and open questions with free text boxes.

Comparable surveys have achieved response rates ranging from 39% to 86% [25, 26]. Even a low response rate would mean a viable study, however, the main aim is to generate an understanding of different models and different types of implementation, rather than to achieve a highly representative sample. More important is diversity in context–data from different UK nations and different size local authorities–to capture variation. Additional aims are to make initial contact with practitioners who can form a community of practice for help in delivering WP2 and to identify local authorities where FGCs are not offered for WP3.

*Data analysis*. Descriptive statistics on survey responses will be produced using Stata software. Free text responses will be thematically synthesised.

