*Sampling and research participants*. We have identified two FGC sites with contrasting contexts in which to conduct consultation workshops in London and North Wales. Both areas have FGC services with strong track records of service delivery and ongoing family involvement. These are the Camden Family Group Conference Service and Y Bont, based near Caernarfon. The two areas are contrasting in several respects. Camden is an inner city, multi-ethnic London borough. North Wales–Y Bont serves Gwynedd, Conwy, and Denbighshire local authorities–is a mixture of smaller towns and rural areas, mostly White and containing a high proportion of Welsh language speakers, especially in Gwynedd. Camden and North Wales both have pockets of extreme deprivation. From each of these areas we have recruited a peer researcher with experience of having taken part in FGCs as a family member. These staff were recruited with the help of FGC services in the two sites. They are full members of the research team and will take part in all aspects of WP1, but with particular responsibility for setting up and running the consultation with family members. They are supported by the CASCADE research centre’s framework for employing people with lived experience of social care.

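### The WP1 survey gives authorities with family group conferences more ways to answer than those without, so provision is likely to be overstated and WP3 control authorities under-found

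*Protocol article*

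**What the plan says.** The Introduction sets the question: "RQ1: What is the extent and nature of FGC provision for child welfare in the UK". In WP1 part A (Identification of FGC services in the UK) the sample frame is "all local authorities in England, Scotland and Wales, and Health and Social Care Trusts in Northern Ireland (n = 212"), and the text says it wants to hear from authorities that never used FGCs or have withdrawn from them.

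The Data collection paragraph then states: "There are two routes to reaching FGC services". The first route sends the link to all heads of children's services, and the team will "ask them to cascade the survey to relevant staff, such as FGC service managers". The second is a web search for independent FGC services, which are then emailed. FGC service managers are the expected respondents, although anyone may complete the form. Ten topics are listed. The first two are whether FGCs are used now and whether they were offered in 2017-19. The other eight concern an FGC service and how it works.

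Part A cites response rates of 39% to 86% in comparable surveys. It says a low rate is acceptable because the main aim is to understand models of practice rather than to be highly representative. It adds a further aim: to "identify local authorities where FGCs are not offered for WP3". The WP3 sampling section names this survey, and no other source, as where the comparison authorities will be found. The quantitative analysis is one sentence: "Descriptive statistics on survey responses will be produced using Stata software".

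**The concern.** Two of the survey's uses turn on authorities that do not run FGCs: the share of authorities with provision, and the list of potential WP3 control authorities. The fieldwork is built around FGC services. A provider can be reached twice and has an obvious person to reply. A non-provider can be reached once, through a request to pass the link to staff it may not have, for a form most of which does not apply to it. If providers answer more readily for these reasons, the observed share rises above the true one, and the non-providers that do reply are a self-selected minority.

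The disclaimer on representativeness suits a description of practice among providers. It does not carry over to an extent figure or to finding non-providers.

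A second issue is the unit. A response is not the same thing as an authority. One authority may have both its own and a commissioned service, and one service may cover several authorities: "Y Bont serves Gwynedd, Conwy, and Denbighshire local authorities". The article does not say how responses become authorities. The statistical analysis plan it promises is for WP2 and WP3, not for this survey.

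**Working it through.** The protocol gives no precision or power figure for the survey, so there is no figure to reproduce. The arithmetic below shows how the result depends on quantities the protocol does not state.

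**Inputs**
- Frame: 212 authorities (WP1 part A).
- True provision p = 0.75. This is an assumption, borrowed from the Introduction's three-quarters, which covers England and Wales only and includes authorities still planning a service. It implies 0.25 × 212 = 53 non-providers.
- Overall response R: 39% to 86% (WP1 part A).
- k, the provider response rate divided by the non-provider response rate: assumed, 1 to 3.
- m, the mean number of responses per responding provider authority: assumed.

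**1. Differential response.** Observed share = pk / (pk + 1 − p). Given k, this does not depend on R. Non-providers seen = 53 × R / (pk + 1 − p).

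| k | Observed share | Bias (points) | Non-providers seen, R = 39% | R = 86% |
|---|---|---|---|---|
| 1 | 0.75/1.00 = 75.0% | 0 | 20.7 | 45.6 |
| 1.25 | 0.9375/1.1875 = 78.9% | +3.9 | 17.4 | 38.4 |
| 1.5 | 1.125/1.375 = 81.8% | +6.8 | 15.0 | 33.1 |
| 2 | 1.5/1.75 = 85.7% | +10.7 | 11.8 | 26.0 |
| 3 | 2.25/2.5 = 90.0% | +15.0 | 8.3 | not feasible |

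(At k = 3 and R = 86%, the provider response rate would have to exceed 100%.) The counts are UK-wide. WP3 uses England only, so fewer would be usable.

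**2. Unit of analysis, with equal response.** If responses rather than authorities were counted, the share would be pm / (pm + 1 − p).
- m = 1.25, 1.5 or 2 (several responses per provider authority): 78.9%, 81.8% or 85.7%.
- m = 1/3 (the extreme in which every provider shares one service among three authorities and that service answers once): 0.25 / (0.25 + 0.25) = 50%.

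The unit problem alone therefore has no fixed sign.

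**3. What non-response leaves open, with the authority as unit.** Lower bound = positives / 212. Upper bound = (positives + non-responders) / 212.
- 39% response: 83 authorities, 75% positive = 62.25. Bounds 62.25/212 = 29% and (62.25 + 129)/212 = 90%.
- 86% response: 182 authorities, 75% positive = 136.5. Bounds 136.5/212 = 64% and (136.5 + 30)/212 = 79%.

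**The case against.** The strongest reply is that non-providers are inside the design. All 212 authorities are in the frame, every head receives the link, FGC managers are only an example of suitable staff, anyone may answer, and the two items that matter are already on a fairly brief form. That stands. A reader might infer that the survey goes only to FGC services, and the documents do not support that. What remains is an unequal chance of reply, not exclusion.

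It can also be said that the direction is not demonstrated. That stands too: equal response gives no bias, and no response rates by provider status are stated.

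On the unit, the article calls this a survey of local authorities and asks about use in the authority. A reader might infer that percentages will be taken over raw responses, but one condensed sentence does not establish that, and it does not exclude tabulation by authority. The three-authority service in North Wales would, if counted once, lower the figure rather than raise it.

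Finally, harm to WP3 is not shown. The plan asks for at least 1000 control families and gives no minimum number of control authorities, so the counts above cannot be judged short of a need. Overstated provision would not in itself bias WP3.

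The disclaimer on representativeness is the weakest part of the reply, because it addresses neither the word extent in the research question nor the search for non-providers.

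**Conclusion.** The point holds as a likely weakness that is cheap to remedy. The cascade instruction and the second route are stated choices that favour providers, while two stated uses of the survey need non-providers. Provision is therefore likely to be overstated, and the control authorities found are likely to be fewer and self-selected.

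The size is conditional. With true provision assumed at 75%, the overstatement is nil at a response ratio of 1, about 7 points at 1.5 and about 11 points at 2. It would be wrong to read any of these as the expected bias, since the ratio is an assumption and 75% is itself a rough base. The absence of a stated authority-level unit adds uncertainty in either direction. For WP3 the consequence is a smaller, self-selected pool of control authorities, which matters because the WP3 model has local authority random effects. It is not a demonstrated bias in the WP3 estimate.

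**What to change.** - Ask each head of children's services to answer the two existing items (FGCs used now; offered in 2017-19) directly, as a yes/no nil return, when there is no FGC service to pass the survey to. Chase that return separately from the full questionnaire.
- Before analysis, reduce all returns to one reconciled record per authority. Merge several answers from one authority, assign a multi-authority service to each authority it covers, and settle conflicts with the head's office.
- Report provision out of 212, show non-responders as unknown, and give the lower and upper bounds set out above.
- Confirm non-provision in 2017-19 for each English authority used as a WP3 control.

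The addressees are already being emailed and the items are already written, so the cost is some extra chasing and data cleaning. If response stays low the bounds will be wide (29% to 90% at 39% response with 75% positive). That is uncomfortable to report, but it states fairly what the survey can say about extent.
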